### Evaluation of hypoglycemia

Hypoglycemia is defined using the following criteria: 1) asymptomatic hypoglycemia (if blood glucose is measured as <70 mg/dL without clinical symptoms); 2) symptomatic hypoglycemia (the symptoms of hypoglycemia (e.g., sweating, severe hunger, shivering, and panic) including blood glucose level < 70 mg/dL or not confirmed); 3) daytime hypoglycemia (7 am-11 pm; hypoglycemia before sleep after the wake-up); 4) nocturnal hypoglycemia (11 pm-7 am; hypoglycemia from sleep to wake-up); 5) severe hypoglycemia (help is needed to restore glucose level). If subjects have hypoglycemia meeting the above criteria, they use the hypoglycemia diary in the PHR app to record the details of the hypoglycemic event. At each clinic visit at weeks 12 and 24, the incidence and type of hypoglycemia are identified and recorded via face-to-face interview.

### Evaluation of the stability of ICT-based centralized clinical trial monitoring

At week 12 and 24 clinic visits, the CRC will identify the frequency of hypoglycemia, insulin dose, body weight, and blood pressure in the face-to-face interview; analyze the consistency of the data examined by the CRC and transmitted data from the PHR app, including the hypoglycemia diary; and verify the efficacy of the ICT-based centralized clinical trial monitoring. The satisfaction questionnaire about the DTSQ and ICT-based centralized clinical trial monitoring will be evaluated.

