**Fig. 1 Fig1:**
[figure not shown]
Information and communication technology-based centralized monitoring system. The CRC registers the subject in the integrated management system, registers personalized conditions such as target blood glucose, and logs in the personal health record app through the newly created user ID and password. The PHR app sends login information to the home monitoring system and returns the survey ID. The home monitoring system receives user information (personal information, screening number, etc.) from the integrated management system. The PHR app sends login information and survey ID to the hospital monitoring system and automatically registers the patient. The CRC registers personalized conditions, such as target blood glucose and subject classification, in the hospital monitoring system. Blood glucose values by glucometer, step count by Samsung Health app, insulin regimen, hypoglycemia diary, and food diary inputted by the patient are transmitted to the home and hospital monitoring systems through the HL7 v2 message. Based on the received blood glucose values, the hospital monitoring system sends an algorithm-based feedback message, and the PHR app shows the feedback message. The PHR app that receives the feedback message transmits the HL7 v2 message to the home monitoring system. All information and feedback messages saved in the home monitoring system are stored in the eCRF. ﻿*CRC* Clinical research coordinator, *PHR* Personal health record

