### ICT-based centralized clinical trial monitoring system

A centralized clinical trial monitoring system based on ICT allows the investigators to store and retrieve personal medical information transmitted from a medical device at an out-of-hospital location (e.g., at home) and to obtain reliable clinical data. This system is expected to be useful for clinical decision making (Fig. 2). The ICT-based centralized clinical trial monitoring system for clinical trials used in this trial consists of 1) a PHR application that acts as a gateway to identify the subjects of the clinical trial and transmit biometric information to the server; 2) at-home measurement device (Bluetooth-enabled blood glucometer); 3) a home monitoring system server where transmitted data is stored, monitored, and transferred; 4) an electronic case report form (eCRF) system (EDC) that extracts and implements the data necessary for clinical trials from the home monitoring system data; and 5) an integrated management server, in which all the above data are collected and managed. The at-home measurement device required for this clinical trial is a blood glucometer linked with Bluetooth, which measures and transmits blood glucose levels to the PHR application with every measurement. Therefore, syncing to the PHR application with Bluetooth is required to save and transmit data to the server automatically. The step count taken per day acquired by the Samsung Health application (Samsung Electronics, Korea) is automatically linked to the PHR application. The Android-based ‘PHR app,’ having recently developed new functions making it capable of interoperability with a wide range of devices, transmission of PHR data to a clinical trial server, and a graphic interface for providing information to medical staff, will be applied for this clinical trial. In addition, subjects can record their insulin protocol, food diary, and ‘hypoglycemia diary’ in the PHR app. The home monitoring system accumulates transferred biometric data, including blood glucose levels measured from the at-home measurement device, step count, and recorded data, including insulin regimen, food diary, and hypoglycemia diary for each registered subject through an integrated management system and transmits the data to the eCRF system via HL7 v2 message, a standardized protocol. For the ICT-based intervention group, PHR app information is sent to the investigator web page in the home monitoring system, and the investigator can view the subject’s data. In addition, algorithm-based feedback messages are transmitted to investigators, as well as subjects in the ICT-based intervention group when blood glucose level is not within the target range. Push feedback messages generated by the home monitoring system server will be displayed on the screen of the subject’s PHR app. eCRF is necessary for inputting and storing clinical trial data for each visit per subject through the integrated management system. Only the investigator or designated person can access the eCRF system to input, store, and examine a subject’s data. The Clinical trial management system (CTMS) is a superordinate system for managing all data, from subject registration and randomization, for transmitting data to the home monitoring system and eCRF and for integrating and managing all data for each measurement per subject. In addition, the CTMS is responsible for the management of participating institutions and investigators, monitoring, and adverse reaction monitoring and reporting. For system data security, the PHR app, the investigator web page, the home monitoring system, the eCRF system, and the integrated CTMS all protect personal medical information and maintain high standards of confidentiality by system log recording methods through automatic logoff, control and authentication on access, data encryption, and data audits.

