### Data acquisition and evaluation

For all subjects, at each clinical visit, anthropometric parameters, current medication use (including types of insulin and insulin dose), hypoglycemic events, vital signs, body composition, questionnaire for satisfaction with the investigation, and any adverse events are examined, and blood tests are performed. The mean duration of medical consultations by a doctor at an outpatient clinic and the number and mean duration of telephone counselling calls by diabetes educators are also evaluated. Prior to the post-interventional clinical visit at weeks 12 and 24, a clinical research coordinator (CRC) will check whether subjects continuously run and synchronize their PHR apps, the number of synchronizations, transmitted data of insulin dose, parameters regarding hypoglycemia and the 3-day food diary, and the measured number of steps taken during weeks 1–12 and weeks 13–24 in both intervention groups. For the ICT-based intervention group, the CRC will identify the types of algorithm-based feedback messages, whether subjects act on the feedback, and the recorded data from the hypoglycemia diary.

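### The coordinator role sees the app's insulin-dose and hypoglycemia data before the interview it is compared with, and body weight and blood pressure have no app value to compare

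*Protocol article*

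**What the plan says.** Confirming the validity and stability of the ICT-based monitoring system is the second half of the study aim (protocol article, Abstract and end of *Background*). *Economic evaluation of ICT-based centralized clinical trial monitoring* adds that the same individuals are assessed by two routes for this purpose.

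The comparison is described in *Evaluation of the stability of ICT-based centralized clinical trial monitoring*. At the week 12 and 24 visits "the CRC will identify the frequency of hypoglycemia, insulin dose, body weight, and blood pressure in the face-to-face interview". The sentence continues that the CRC will "analyze the consistency of the data examined by the CRC and transmitted data from the PHR app, including the hypoglycemia diary".

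*Data acquisition and evaluation* describes an earlier step: "Prior to the post-interventional clinical visit at weeks 12 and 24, a clinical research coordinator (CRC) will check" a list of things in both groups. Besides synchronization and step count, that list contains "transmitted data of insulin dose, parameters regarding hypoglycemia and the 3-day food diary". For the ICT-based group it adds that "the CRC will identify the types of algorithm-based feedback messages, whether subjects act on the feedback, and the recorded data from the hypoglycemia diary".

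The transmitted data are set out in the caption of Fig. 1: "Blood glucose values by glucometer, step count by Samsung Health app, insulin regimen, hypoglycemia diary, and food diary inputted by the patient are transmitted". *ICT-based centralized clinical trial monitoring system* gives the same streams: glucose and step count, plus "recorded data, including insulin regimen, food diary, and hypoglycemia diary for each registered subject". The one home measurement device it names as required is the Bluetooth glucometer. *Anthropometric and vital sign measurements* places body weight and blood pressure at clinic visits 1, 3 and 4.

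**The concern.** A consistency check between two data sources tests something only if the second reading is taken without knowledge of the first. Here the role that elicits hypoglycemia frequency and insulin dose is also the role that has just looked at the app's values for them, and it then judges whether they agree. An interviewer who knows that the app shows three low readings can prompt until three are recalled, without any intent to bias. The trial could then report that its monitoring system is valid on the strength of an agreement that the procedure itself helped to produce. Bias that enters when data are collected cannot be removed in analysis.

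Separately, a comparison listed for weight and blood pressure needs an app value on the other side, and none is described.

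**Working it through.** **Plan's own figure.** No figure is given for the consistency analysis: no expected agreement, threshold or precision. The only design figure is the sample size for the primary outcome, and it reproduces. With 55% versus 88%, mean 0.715, difference 0.33, two-sided 0.05 and 90% power:

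n = [1.96·√(2·0.715·0.285) + 1.2816·√(0.55·0.45 + 0.88·0.12)]² / 0.33² = (1.251 + 0.762)² / 0.1089 ≈ 37.2, rounded up to 38 per group. Then 38 / (1 − 0.20) = 47.5, rounded up to 48.

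Nothing in this point alters it.

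**Step 1: order of tasks and pairing of items.** The four items in the interview list, set against the pre-visit check and the transmitted data:

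| Interview item | Seen by a CRC before the visit | Transmitted by the app |
|---|---|---|
| Hypoglycemia frequency | Yes (hypoglycemia parameters) | Yes (hypoglycemia diary, glucose) |
| Insulin dose | Yes | Yes (insulin regimen) |
| Body weight | Not listed | Not listed; no home device named |
| Blood pressure | Not listed | Not listed; no home device named |

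Two of the four items can be compared, and both are on the list viewed beforehand. The other two have no counterpart. As described, no item is both comparable and free of prior sight.

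**Step 2: is there a safeguard elsewhere?** *Evaluation of hypoglycemia* requires a face-to-face interview but does not say who conducts it or what that person has seen. *Data monitoring* and *Audit* do not address it. The article states no separation of staff and no rule that the interview is entered first.

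**Step 3: how far could prior sight move agreement?** This is an illustration only; every input is an assumption. Let π be the share of subjects with any hypoglycemia by the app, Se and Sp the sensitivity and specificity of an unaware interview against the app, and q the share of discrepancies brought into line with the app value.

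- Both yes: a = π[Se + (1 − Se)q]
- Both no: d = (1 − π)[Sp + (1 − Sp)q]
- Observed agreement: Po = a + d
- Interview yes: m = a + (1 − π) − d
- Chance agreement: Pe = πm + (1 − π)(1 − m)
- κ = (Po − Pe)/(1 − Pe)

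With π = 0.5, Se = 0.7, Sp = 0.9:

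- q = 0: Po = 0.35 + 0.45 = 0.80, m = 0.40, Pe = 0.50, κ = 0.60
- q = 0.5: Po = 0.425 + 0.475 = 0.90, m = 0.45, Pe = 0.50, κ = 0.80

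Over π = 0.3 and 0.5, with (Se, Sp) = (0.7, 0.9) and (0.8, 0.95):

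| q | κ |
|---|---|
| 0 | 0.60 to 0.77 |
| 0.25 | 0.70 to 0.83 |
| 0.50 | 0.80 to 0.89 |
| 0.75 | 0.90 to 0.94 |

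The direction is always upward. The size depends wholly on q, about which the documents say nothing.

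**The case against.** **The text names a role, not a person.** At two sites the CRC who checks the app and the CRC who interviews may differ, and the pre-visit step may partly be a completeness check. This stands. A reader might infer that agreement will certainly be inflated; the article supports only that it is liable to be, because nothing prevents it.

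**The comparator may be wider than the interview.** The economic evaluation section speaks of questionnaire or medical-record evaluation, and insulin dose is also examined as current medication at each visit. A dose taken from the medical record would not depend on what the CRC had seen. That could soften the point for insulin dose, but the stability section itself sets the CRC's own data against the app's.

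**Weight and blood pressure may be loose drafting.** The sentence can be read as comparing only what the app transmits. Two unpaired items then inflate nothing. This is fair, and it means that a reader should not conclude that the whole validity result is impossible to obtain; that description fits these two items alone. The mention of interoperability with many devices describes the app's capability and supplies no scale or cuff in this trial.

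**Both sources come from the same patient.** The patient enters the diary and answers the interview, so the two are related whatever the CRC has seen. True, but this is a limit on any such comparison and no reason to add a second, avoidable dependence.

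**The two arms might be affected differently.** The review of hypoglycemia diary records is stated only for the ICT-based group, so one might infer unequal ascertainment of hypoglycemia between arms. That sentence does not repeat the pre-visit timing, and hypoglycemia parameters are checked beforehand in both groups, so the inference is not established.

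**Consequence.** Validity is a stated aim, but it is not among the hypotheses, and consistency is not a listed outcome. Which agreement statistic to use can be left to the analysis plan and is not part of this point.

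**Conclusion.** The point holds in limited form. As sequenced, the comparison for hypoglycemia frequency and insulin dose is not protected from prior knowledge of the app values, and agreement on both is liable to be overstated by an unknown amount. The κ ranges above show what could happen under assumed inputs; they are not estimates for this trial. For body weight and blood pressure, no agreement can be computed from the data streams described. This rests on reading the data examined by the CRC as the four items just listed, and on the Fig. 1 caption and the system description as the account of what is transmitted. The matter is confined to the aim concerning the monitoring system. It should be corrected because the change is cheap and the dependence cannot be undone afterwards.

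**What to change.** 1. Keep the pre-visit check for synchronization, step count, food diary, and the presence or absence of insulin-dose and hypoglycemia records. A ban on all content checks would go too far: the primary outcome uses basal doses from the last 7 days before visit 3, so completeness of dose records must still be checked in time.
2. Have the interview values for hypoglycemia and insulin dose entered and locked in the eCRF before the interviewer sees the transmitted values of those two items. Alternatively, let existing staff who have not seen them do the interview. For hypoglycemia the second option is cleaner, since knowing that a diary record exists already hints at an event.
3. Limit the agreement analysis to items with an app source by removing body weight and blood pressure. Both remain clinic measurements and secondary outcomes.

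The cost is a change in the order of tasks and an eCRF lock, with no added visits, subjects or staff. The small downside is that discrepant or implausible dose or diary values can be queried only after the interview entry is locked.

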### Economic evaluation of ICT-based centralized clinical trial monitoring

Expenses associated with ICT-based centralized monitoring system and costs for additional admission, outpatient clinical examination, and transportation by insulin dose adjustment training based on PHR apps in both two groups will be evaluated. The same individuals will be analyzed twice using ICT-based and questionnaire/medical record-based evaluation to confirm the stability and validity of the ICT-based centralized clinical trial monitoring system.

### Discontinuation of subjects

Discontinuation of subjects comprises withdrawals as requested by the subject or by the investigator, loss to follow-up, and death. In addition, discontinuation of subjects also includes the cases in which the subject has experienced an adverse event that requires early termination because continued participation imposes an unacceptable risk to the subject’s health or the subject is unwilling to continue because of the adverse event. The reason for withdrawal or discontinuation of the subject from the study should be recorded in the eCRF. The investigator and site staff compile the case records, clinical trial progress, and results of the study performed until the time of discontinuation.

### Adverse event assessment and safety follow-up

At each televisit and clinical visit, concomitant medications and adverse events / severe adverse events will be inquired and assessed. The investigator or site staff will be responsible for detecting, documenting, and reporting on adverse events/ severe adverse events using the respective adverse event page in the eCRF. Investigators must report all new severe adverse events or pregnancies for which they have been notified at the safety follow-up.

### Data monitoring

The clinical research assistant (CRA) will conduct data monitoring to ensure that the human rights and safety of the study subject are being protected, the clinical trial is conducted in accordance with the approved clinical trial protocol and applicable regulatory requirements, and data are accurate, authentic, and complete, independent from competing interests. Monitoring should be carried out when it is necessary to check the CRF created at the time of each patient registration and to check the progress of the study. Periodic monitoring is performed after the first patient is registered for each institution to ensure the quality and reliability of clinical trial results.

### Audit

Any aspect of the clinical trial may be subject to audits to assure compliance with the KGCP and related regulations regarding the collection, recording, documentation and reporting of clinical trial data. The investigators and the site staffs should cooperate with the activities of CRA and give internal and external auditors direct access to all source documents at the trial site to examine, analyze, verify any records and reports relevant to the clinical trial. According to the results of the investigation, the investigator and site staff have an obligation to supplement and correct the clinical trial-related documents and immediately take the appropriate action. Any records and reports from the clinical trial must be retained at research institute for at least 10 years after completion of the study.

### Data analysis

All continuous variables will be presented as mean ± standard deviation, and categorical variables will be presented as frequency and proportion. For analyzing primary outcomes, the percentage of patients who reached the optimal insulin dose within 12 weeks is presented, and the difference between the two groups is compared using Pearson’s chi-square test or Fisher’s exact test if the frequency is low (<5). Differences are analyzed using Pearson’s chi-square test or Fisher’s exact test for categorical variables and Student’s t-test or Wilcoxon’s rank-sum test for continuous variables of secondary outcome variables. Comparisons between the two groups will be performed using a stratification analysis based on the use of pre-prandial insulin two or more times per day and each research institute. Prespecified subgroup analyses, including use of immunosuppressants (including steroids); type of DM; HbA1c >9%; use of pre-prandial insulin; aged over 65, 60, or 55; type of basal insulin; and stage of chronic kidney disease at baseline are performed. For handling missing data, last-observation-carried-forward (LOCF) imputation method would be performed.

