### Outcome variables

The primary outcome will be the proportion of patients who reach the optimal insulin dose within 12 weeks of enrolling in the study, without severe hypoglycemia or unscheduled visits to the clinic. Achievement of the optimal insulin dose is defined as follows: A. For a patient who uses basal insulin only or basal insulin with pre-meal rapid-acting insulin once per day, 1) three or more fasting blood glucose values within the target range (80 to 130 mg/dL or 100 to 140 mg/dL) during week 12 (last 7 days prior to visit 3), 2) no nocturnal (from 11 pm to 7 am) or pre-breakfast hypoglycemia (<70 mg/dL) during week 12, and 3) variation of basal insulin dose (defined as the difference between the highest and lowest basal insulin doses) <10% of the mean total basal insulin dose during week 12. B. For a patient who uses multiple daily injections, including basal insulin with pre-meal rapid-acting insulin at least twice per day, the criteria are those in A plus 4) three or more days in which the correction dose of pre-meal insulin is required less than three times per day during week 12, and 5) no daytime (from 7 am to 11 pm) hypoglycemia (<70 mg/dL) during week 12.

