### Interventions

#### Randomization

Educators provide telephone counseling after the 1-week run-in period. Before the telephone counseling, investigators check the synchronization of the at-home measurement device and the PHR application through the web page for administrators. For those who are suitable for the clinical trial based on daily synchronization, block randomization will be performed. The subjects will be randomly allocated to an intervention with ICT-based centralized monitoring or not, at a ratio of 1:1, per the Interactive Web Response System (IWRS). The randomization is stratified according to the research institute (Samsung Changwon Hospital: Samsung Medical Center = 20:76) and the use of pre-prandial insulin two or more times per day.

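### The primary outcome has an unstratified test and an unranked, unnamed stratified analysis, although randomisation is stratified and the endpoint is harder to meet in one stratum

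*Protocol article*

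**What the plan says.** Three parts of the protocol article bear on this point.

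- **Randomization.** "The randomization is stratified according to the research institute (Samsung Changwon Hospital: Samsung Medical Center = 20:76"), with a second factor, "the use of pre-prandial insulin two or more times per day".
- **Outcome variables.** The definition of an optimal dose divides at the same regimen boundary. Patients on basal insulin, alone or with one pre-meal injection a day, must meet three criteria (definition A). For patients with at least two pre-meal injections a day (definition B), "the criteria are those in A plus 4") and 5): a limit on correction doses and no daytime hypoglycaemia in week 12.
- **Data analysis.** For the primary outcome, "the difference between the two groups is compared using Pearson’s chi-square test or Fisher’s exact test if the frequency is low (<5"). Two sentences later: "Comparisons between the two groups will be performed using a stratification analysis based on the use of pre-prandial insulin" (at least twice daily), with institute as the other factor. The section does not say whether this second analysis replaces the crude test, supports it or only shows results by stratum, and it names no stratified method.

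**The concern.** Stratified allocation removes chance imbalance on the stratification factors, so the true variance of the difference in proportions contains only the within-stratum part. The crude Pearson test estimates its variance from the pooled success rate, which also contains the between-stratum part. If success differs between strata, the crude standard error is too large, the test rejects less often than its nominal level, and some power is given up.

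There is a structural reason to expect a difference here. At the same level of glucose control, a patient under definition B can do no better than one under definition A, because two more conditions must hold. The documents give the direction but not the size.

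The second issue is which result is primary. The section commits to two analyses of the same comparison and ranks neither. If they fall on opposite sides of 0.05, the text does not say which one decides.

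**Working it through.** **1. The plan's own sample size.** Inputs from Sample size assumptions: 55% v 88%, two-sided alpha 0.05, power 90%, dropout 20%. With the unstratified, pooled-variance formula:

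- Mean rate = (0.55 + 0.88)/2 = 0.715. Null term: 1.960 × √(2 × 0.715 × 0.285) = 1.960 × 0.6384 = 1.251.
- Alternative term: 1.2816 × √(0.55 × 0.45 + 0.88 × 0.12) = 1.2816 × 0.5942 = 0.7615.
- n = (1.251 + 0.7615)² / 0.33² = 37.2, so 38 per group. Then 38/(1 - 0.20) = 47.5, so 48 per group and 96 in all.

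Both stated figures reproduce. The planned power therefore already refers to the crude test, and the formula gives 90.6% at 38 per group.

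**2. Type I error of the crude test.** Assumptions that are not in the documents: a share f of patients in the harder stratum, a success-rate gap g between strata, and exact 1:1 balance within strata. Under no effect, with both arms at 55%:

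- Pooled variance = 0.55 × 0.45 = 0.2475. Between-stratum part = f(1 - f)g².
- The crude z then has standard deviation r = √(1 - f(1 - f)g²/0.2475), and the type I error is 2 × [1 - Φ(1.960/r)].
- Example, f = 0.5 and g = 0.40: 0.25 × 0.16 = 0.04; r = √(1 - 0.04/0.2475) = 0.9156; 1.960/0.9156 = 2.141; type I error 0.032.

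| Gap g | Formula, f = 0.5 | Simulated crude, f = 0.5 | Formula, f = 0.3 | Simulated crude, f = 0.3 |
|---|---|---|---|---|
| 0.10 | 0.0488 | 0.0497 | 0.0490 | 0.0482 |
| 0.20 | 0.0454 | 0.0439 | 0.0461 | 0.0460 |
| 0.30 | 0.0398 | 0.0393 | 0.0414 | 0.0412 |
| 0.40 | 0.0323 | 0.0319 | 0.0350 | 0.0352 |

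(200,000 runs per row, 38 per arm.) The CMH test stays between 0.046 and 0.050 in the same runs.

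**3. Power at the planned rates.** Marginal rates held at 55% and 88%, 38 per arm, with the gap in the intervention arm assumed to be half that in the control arm:

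| Control-rate gap | Crude Pearson, f = 0.3 / 0.5 | CMH, f = 0.3 / 0.5 |
|---|---|---|
| 0 | 91.7% / 91.7% | 91.4% / 91.4% |
| 20 points | 91.9% / 91.9% | 92.1% / 92.1% |
| 30 points | 92.3% / 92.5% | 93.1% / 93.3% |
| 40 points | 92.7% / 93.1% | 94.2% / 94.7% |

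The change runs from about -0.3 to +1.6 points. At 48 per arm it is at most +0.8. Using four strata (assumed 15, 15, 4 and 4 per arm for site by regimen, with no site effect) leaves the picture unchanged: with gaps of 0, 20 and 40 points, crude v CMH is 91.7% v 91.5%, 92.0% v 92.3% and 93.2% v 94.7% (400,000 runs).

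**4. Where larger gains appear.** Two equal strata, 48 per arm, 400,000 runs:

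- 90% v 70% in one stratum and 50% v 20% in the other: crude 73%, CMH 81%. The tests disagree on significance in 8.3% of trials.
- 85% v 65% and 55% v 25%: crude 72%, CMH 77%. They disagree in 4.7%.

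Both scenarios average 70% v 45%, a 25-point effect against the planned 33, and assume stratum gaps of 30 to 50 points.

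**The case against.** The strongest reply is that the Data analysis section already provides a stratified comparison on exactly the randomisation factors, and that one natural reading applies it to every group comparison, the primary included. On that view only the method's name and rank are missing, and an article may leave those to the SAP. This stands in part: a reader who infers that the plan ignores stratification goes too far. But the same section names a crude test specifically for the primary outcome, and nothing says that the later sentence overrides it. A SAP would have to choose between two statements already made.

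The second reply is that the crude test is valid, errs only on the safe side and meets the planned power. That stands. A reader might infer from the 73% v 81% figures that the trial is underpowered. The documents do not support this: those figures need a smaller effect than planned and large assumed gaps, and 38 per group was derived for the crude test. Nor do two extra criteria show that the stratum is strongly prognostic.

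A reader might also object to the switch to Fisher's test at low counts. Read as observed cells below 5, the exact power at 38 per arm is 0.911 with the switch and 0.917 for Pearson alone. That is too small to be a separate argument.

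**Conclusion.** The point holds in limited form. The named primary test does not reflect the stratified allocation, the stratified analysis beside it has neither a method nor a rank, and the endpoint definition gives a reason to expect lower success in one stratum. The consequence is mild conservatism: type I error of about 0.045 to 0.032 for assumed gaps of 20 to 40 points, and close to nominal at 10 points or less. No false-positive risk arises, and the stated 90% power is met either way. The choice of test matters most if the effect turns out smaller than planned and the strata differ widely, because the two analyses are then most likely to disagree.

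The sizes rest on assumed stratum shares of 30% and 50%, assumed gaps and exact balance within strata. The documents give no rates by regimen or by site.

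**What to change.** State in the Data analysis section or the SAP, before any outcome data are compared, that the primary test is the CMH test stratified by site and by pre-prandial insulin two or more times a day, using the strata as randomised. Report a stratified risk difference with its 95% CI. Keep the crude Pearson or Fisher result as a supportive analysis. This also gives the existing sentence on stratification a definite meaning and settles which p-value is primary.

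The cost is one sentence. The sample size does not change. If the strata prove not to be prognostic, the loss is about 0.3 points of power at 38 per arm.
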